#### Recruitment of patients

At each practice site, the lead GP or practice nurse for diabetes is responsible for managing patient recruitment. During the data collection period, all adult patients with type 2 diabetes with an impending review appointment who meet the inclusion criteria will be contacted by post and invited to participate within the study. Participation and consent are subsequently discussed with the referring GP or nurse at the review appointment. Hence, the intention is that the intervention should be implemented systematically within the normal practice routine, as far as possible. Patients will be provided with written information about the study, and invited to give written consent for inclusion.

### Experiments Proposed Including End Points

The hypotheses to be tested are that the telecare intervention compared with routine care alone will improve adherence to the change in medication targeted; improve clinical and psychological status; encourage healthier lifestyle choices and enhance satisfaction with care. In addition, that it will be acceptable to patients and primary care health professionals.

#### Baseline Data

In addition to the questionnaires outlined below, for patients who consent to be randomised, sex, age, ethnicity, diabetes history, most recent clinical parameters (HbA1c, BP, BMI, total plasma cholesterol, HDL: total cholesterol ratio, and plasma triglycerides), prescribed medication, smoking status, phone number, access hours, and any provisos requested by the patient will be recorded on a pro forma at recruitment by practice staff. Patients who do not wish to participate in the study will be asked for consent to include their reasons for not doing so, and their sex, age, ethnicity, most recent clinical parameters and smoking status will be recorded. This will allow for comparison between the characteristics of participants and non-participants.

#### Outcome Data

All outcome data from patients in the intervention and control groups are being collected at site level by a practice nurse or GP, recorded on templates developed for the purpose, and forwarded by post to the trial office. Patients in the intervention groups will be asked to complete a 4 page questionnaire after 3 and 6 months, while patients in the control group will complete the questionnaire only at 6 months. The questionnaire incorporates The Problem Areas in Diabetes Scale (PAID) [24], the Diabetes Management Self-Efficacy Scale (DMSES) [25], the diabetes self-care activities measure [26], the Perceived Therapeutic Efficacy Scale (scale under development) [27], and an acceptability of service provision measure. The questionnaire will be completed at the surgery and posted in a reply paid envelope.

#### Clinical Data

Clinical data at baseline will be collected prior to patient randomisation. Blood specimens for HbA1c assessment, total and HDL cholesterol are being taken according to local protocols either by practice staff or the local phlebotomy service. They are being analysed by the local hospital based laboratory services routinely used by the practices, blinded to patient group allocation. We will ensure that if changes in standardisation occur during data collection that, at each site, all data are reported according to the same standard. Practices will arrange a 3 and 6 month review appointment with patients in the intervention group and a 6 month review for those in the control group at which point clinical follow up data will be collected. A reminder of forthcoming appointments will be distributed by the trial office to each participating practice 2 weeks before the appointment is due.

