## Methods/Design

This study is an RCT of three arms:

i. Telecare service provided by diabetes specialist nurses

ii. Telecare service provided by peer supporters

iii. Control group receiving routine care only

Randomisation to control or intervention will be carried out at the patient level. Within the intervention group, patients will be randomly allocated to either a nurse or peer telephone supporter. To limit bias arising from patients' perception of their randomisation, all patients will receive at least one phone call. This should also ensure that the referring healthcare practitioners are as blinded as realistically possible. Patients will not be informed about whether they are in the intervention or control groups. The name, address, telephone number, access times, current treatment, details of any recent change in therapy (medication, diet, monitoring, and physical activity programme) related to diabetes, together with any provisos that were made, will be sent to the trial centre by the referring GP/nurse.

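### Both telecare arms get a 3-month practice review and questionnaire that controls do not, so the 6-month telecare-versus-control differences cannot be separated from the effect of that extra contact

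*Protocol article*

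**What the plan says.** The schedule differs by arm in two places in the protocol article.

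- Clinical Data: "Practices will arrange a 3 and 6 month review appointment with patients in the intervention group and a 6 month review". The single 6-month visit named last is the one that controls receive. Clinical follow-up data are collected at these appointments.
- Outcome Data, on the telecare arms: "Patients in the intervention groups will be asked to complete a 4 page questionnaire after 3 and 6 months". That section gives the comparison arm a single administration: "patients in the control group will complete the questionnaire only at 6 months". This questionnaire contains the DMSES, the primary outcome measure, and the self-care activities measure.

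Outcome data are "collected at site level by a practice nurse or GP, recorded on templates developed for the purpose". The trial office prompts the practice for each visit: "A reminder of forthcoming appointments will be distributed by the trial office to each participating practice 2 weeks before the appointment is due".

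Aims of the Trial sets the comparison as nurse and peer telecare against routine care. Proposed Telecare Service describes telecare as telephone support supplementing routine care and does not list a practice review among its components. Methods/Design arranges a telephone call for every patient, controls included, and says of this: "This should also ensure that the referring healthcare practitioners are as blinded as realistically possible".

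**The concern.** If one side of a randomised comparison is seen and questioned more often than the other, the difference at the endpoint reflects the treatment and the additional contact together. Here the additional contact is a practice review with clinical measurements, halfway to the 6-month endpoint, plus an extra administration of the primary outcome questionnaire.

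The article itself gives a route by which a review could matter. The Discussion says that practices have financial incentives to bring HbA1c below 7.4% by more active prescribing, and all participants enter above that level. One more scheduled review is one more occasion to change treatment. It is not trivial beside an intervention that Proposed Telecare Service puts at about 45 minutes in total.

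The second issue is masking. A reminder for a 3-month visit is sent only for telecare patients, so it tells the practice that the patient is in a telecare arm. The staff who receive it also manage the patient and collect the 6-month data.

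**Working it through.** **Step 1. Contacts by arm, from Outcome Data and Clinical Data.**

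| Trial-arranged after baseline | Nurse telecare | Peer telecare | Control |
|---|---|---|---|
| Practice reviews | 2 (3 and 6 months) | 2 (3 and 6 months) | 1 (6 months) |
| Questionnaires including DMSES | 2 | 2 | 1 |
| Reminders to the practice | 2 | 2 | 1 |

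At planned recruitment, 2 × 125 = 250 patients are scheduled for the extra review and questionnaire, and none of the 125 controls are. No other section schedules a 3-month contact for controls.

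**Step 2. Which comparisons are touched.** The extra review coincides exactly with allocation to telecare. Neither adjustment nor a larger sample can separate the two in nurse versus control, peer versus control or pooled telecare versus control. Nurse and peer arms share one schedule, so the contrast between them is not touched.

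**Step 3. Which outcomes are touched by unmasking.** Laboratories are "blinded to patient group allocation", which covers HbA1c and cholesterol measurement. The patient completes the DMSES. What remains is mainly blood pressure and BMI, measured by practice staff, and how the patient is managed.

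**Step 4. Size.** The plan gives no figure to reproduce for this point, and none from which the size could be computed. Two illustrations follow, both on assumed inputs.

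*DMSES.* Suppose telecare has no effect and the extra contact alone shifts the 6-month score by b standard deviations. Take the stated minimum of 100 per arm and assume a two-sided 5% test (the article does not state sidedness).

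SE = √(1/n₁ + 1/n₂); rejection rate = 1 − Φ(1.96 − b/SE) + Φ(−1.96 − b/SE).

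- One telecare arm versus control: SE = √(2/100) = 0.141.
- Pooled telecare versus control: SE = √(1/200 + 1/100) = 0.122.

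| Assumed b | b as share of the 0.35 target | 100 v 100 | 200 v 100 |
|---|---|---|---|
| 0 | 0% | 5.0% | 5.0% |
| 0.05 | 14% | 6.4% | 6.9% |
| 0.10 | 29% | 10.9% | 12.9% |
| 0.20 | 57% | 29.3% | 37.2% |

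If the shift ran the other way, it would hide an equal amount of real benefit.

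*HbA1c.* If the extra review led to a treatment change in 10% to 30% of telecare patients, each worth 0.5 to 1.0 percentage points, the spurious difference would be 0.10 × 0.5 = 0.05 to 0.30 × 1.0 = 0.30 points. All four inputs are assumptions.

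**The case against.** Several stronger readings are tempting, and the article does not support them.

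- **That the 3-month data have no randomised comparator.** They have none for telecare versus control. But Methods/Design randomises telecare patients between nurse and peer, and Trial Analysis plans to compare those two groups. Both have 3-month data, so that comparison can use them. Dropping the visit would therefore lose something.
- **That the schedule flatly contradicts the blinding statement.** That statement is a qualified aim. The reminder works against it but is not the only leak: under Proposed Telecare Service, controls are told on their call that they are in routine care, and supporters may contact the GP. Equal reminders would close one avoidable route and would not restore masking.
- **That the bias favours telecare throughout.** This is plausible for HbA1c. For DMSES, nothing in the article indicates which way repeated questioning moves the score. The extra contact could also alter dropout in either direction.
- **That controls get no review at all before 6 months.** The zero applies to trial-arranged visits only. The article does not describe what follow-up routine care provides, so the net excess may be smaller than one review per patient.

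There is also a fair argument on proportion. Intervention development and trial design calls the trial exploratory, and the third aim is to judge whether a full-scale trial is worthwhile. Eligibility has already changed once during recruitment, and a further change would leave patients on different follow-up schedules. These points limit the severity and shape the remedy. They do not remove the asymmetry, which is stated outright and is not a detail left to a fuller document.

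**Conclusion.** The concern holds for telecare versus control. As scheduled, the 6-month differences, including the primary one, estimate the effect of telecare together with an additional 3-month review and questionnaire, whereas the stated aim is the effect of telecare alone. The likely direction for HbA1c favours telecare and the direction for DMSES is uncertain. The size cannot be derived from the documents; the figures above only show what assumed shifts would do.

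The effect on masking is narrower. It bears mainly on blood pressure, BMI and patient management, and other routes to unmasking exist. The nurse-versus-peer comparison stands, at 3 months as well as at 6.

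This should be fixed, but it does not undermine the trial as a whole: one of its randomised comparisons is untouched, and the problem can be removed for future patients and disclosed for past ones.

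**What to change.** From now on, use the same data-collection schedule and the same reminders in all three arms. There are two ways to do this.

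- **Collect the same 3-month data from controls.** This costs up to 125 extra questionnaires and reviews, and moves controls slightly away from routine care only. It keeps the 3-month nurse-versus-peer data and adds a 3-month comparison with control.
- **Drop the trial-arranged 3-month review and questionnaire from the telecare arms.** This saves work and leaves controls as they are. The price is the 3-month nurse-versus-peer data. Whatever reviews practices hold as part of routine care are not affected.

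Either way, some patients will already be past 3 months on the unequal schedule. For them, describe the telecare-versus-control estimate as telecare plus an additional 3-month review, report treatment changes by arm, and report results by follow-up schedule so that the two periods can be seen separately. This needs a small amendment and some extra tabulation.

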#### Content of Telecare Intervention

Telecare nurses and peer supporters will record the dates, times and duration of calls made to each patient, and the number of attempts required to make contact with the patient on each occasion. The content of calls made to and received from patients (including referrals) will be downloaded from the electronic template. Patient dropouts and reasons for this will also be recorded.

#### Sample size

The sample size is based upon the primary outcome measure of self efficacy, measured using the DMSES and has been constructed to detect a difference in the primary outcomes of self efficacy perceptions and psychological adjustment. A sample of at least 300 patients (minimum 100 in each arm) has been constructed to detect a difference in self-efficacy scores with an effect size of 0.35, 80% power at a level of 5% significance level [25]. Allowing for an attrition rate of 25% from initial recruitment, we will require 125 subjects in each arm (i.e. 375 participants in total).

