**Methods/Design:**

In a 3-arm RCT, participants are allocated to either an intervention group with Telecare service provided by a Diabetes Specialist Nurse (DSN), an intervention group with service provided by a peer supporter (also living with diabetes), or a control group receiving routine care only. All supporters underwent a 2-day training in motivational interviewing, empowerment and active listening skills to provide telephone support over a period of up to 6 months to adults with poorly controlled type 2 diabetes who had been recommended a change in diabetes management (i.e. medication and/or lifestyle changes) by their general practitioner (GP). The primary outcome is self-efficacy; secondary outcomes include HbA1c, total and HDL cholesterol, blood pressure, body mass index, and adherence to treatment. 375 participants (125 in each arm) were sought from GP practices across West Midlands, to detect a difference in self-efficacy scores with an effect size of 0.35, 80% power, and 5% significance level. Adults living with type 2 diabetes, with an HbA1c > 8% and not taking insulin were initially eligible. A protocol change 10 months into the recruitment resulted in a change of eligibility by reducing HbA1c to > 7.4%. Several qualitative studies are being conducted alongside the main RCT to describe patient, telecare supporter and practice nurse experience of the trial.

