### Aims of the Trial

The hypotheses to be tested in this study are that telecare motivational interviewing will be acceptable to patients and primary care health professionals; will be associated with improved social and psychological status; healthier lifestyle choices; and enhanced satisfaction with care.

We propose to:

1. Determine the impact on quality of care, behavioural change and patient responsiveness of a centralised, expert telecare (nurse and peer-led motivational support by telephone) intervention.

2. Compare the impact of nurse and peer supporter telecare provision against routine care.

3. Obtain clinical data as a means to identifying patterns and trends to be used in conjunction with behavioural change outcomes, in order to determine the value of undertaking a full scale RCT of the cost and clinical effectiveness of the intervention.

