### Trial Analysis

Data will be entered in SPSS. A random 20% of the data will be entered twice to check for discrepancies with the original data. Descriptive methods will be used to demonstrate the consistency of the three groups, describe participant characteristics, to compare the refusers with the study participants and report levels of participation and drop out. Comparison of nurse and peer supporter outcome data, experiences and feedback will be provided. Analysis of variance will be used to evaluate baseline characteristics of participants compared to non-participants, overall significance of improvement across outcome measures, and dropout versus maintainers. For each patient, change in physiological measures from start to 6 months will be calculated and analysed using t-test for matched groups for both intervention and control groups. The magnitude of change in both primary and secondary outcome measures will be estimated and the 95% confidence intervals given. *Formal Statistical Input*: A research fellow in medical statistics will provide statistical support and advice throughout the study.

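### The stated 80% power names no comparison: it fits pooled telecare against routine care, but not nurse or peer support separately, and the attrition allowance leaves fewer than 100 per arm

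*Protocol article*

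**What the plan says.** The Sample size section ties the calculation to one outcome: "The sample size is based upon the primary outcome measure of self efficacy, measured using the DMSES". It sets a floor of 300 patients across the three arms ("minimum 100 in each arm) has been constructed to detect a difference in self-efficacy scores with an effect size of 0.35, 80% power"), at a 5% significance level. It then allows for 25% attrition from initial recruitment and arrives at 125 per arm, 375 in total. The abstract gives the 375 with the same effect size, power and significance level.

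The comparison that carries the 80% has to be inferred from other sections, and they point in different directions:

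- Aims of the Trial, aim 2: "Compare the impact of nurse and peer supporter telecare provision against routine care". This can be read as two separate comparisons with control.
- Experiments Proposed Including End Points: the hypotheses set telecare as a whole against routine care alone, without splitting by supporter.
- Methods/Design: patients are first randomised between control and intervention, and those in the intervention group are then divided between nurse and peer.
- Trial Analysis: analysis of variance is named for the overall significance of improvement across outcomes, and "The magnitude of change in both primary and secondary outcome measures will be estimated and the 95% confidence intervals given".

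**The concern.** A power figure belongs to a particular contrast, test and sidedness. In a three-arm trial with equal arms, the same 300 patients give clearly different power for a pooled contrast (200 against 100), a single-arm contrast (100 against 100) and a three-group test. The plan gives one figure and does not attach it to any of these.

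Aim 2 and the per-arm minimum invite a reader to apply the 80% to each supporter type against routine care. If it does not hold there, a null result for peer support alone would be given more weight than the design can bear. At the target effect, such a comparison would miss about one time in three.

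The move from 100 to 125 per arm also looks like multiplication by 1.25. Allowing for a 25% loss requires division by 0.75.

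**Working it through.** **Inputs from the document.** Effect size d = 0.35, power 80%, significance 5%, 100 analysed per arm, 25% attrition, 125 recruited per arm (Sample size; abstract).

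**Assumptions.** The effect size is a standardised mean difference (SD = 1). There is no baseline adjustment and no multiplicity adjustment. Two-sided 5% is an inference: it matches the 95% intervals in Trial Analysis, but the document does not state it.

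**1. Which readings reproduce 100 per arm?** Normal approximation, with z values 1.960 (two-sided 5%), 1.645 (one-sided 5%) and 0.842 (80% power):

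- Pooled telecare v control, 2:1, two-sided: control n = (1 + 1/2)(1.960 + 0.842)² / 0.35² = 96.1, so 97 control and 194 telecare. Reproduces.
- One arm v control, one-sided: n = 2(1.645 + 0.842)² / 0.35² = 101 per arm. Reproduces.
- One arm v control, two-sided: n = 2(1.960 + 0.842)² / 0.35² = 128.2, so 129 per arm. Does not reproduce.

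**2. Attrition.** 100 × 1.25 = 125, which is the plan's figure. But 125 × 0.75 = 93.75, about 94 per arm, below the stated minimum of 100. In total, 375 × 0.75 = 281, below 300. Keeping 100 analysed needs 100 / 0.75 = 133.3, so 134 per arm (402 in total).

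**3. Power at 100 and at 94 analysed per arm.** For two groups, the noncentral t with ncp = d / √(1/n₁ + 1/n₂). For three groups, the noncentral F with λ = n Σ(mᵢ − m̄)².

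- Pooled at 100: 0.35 × √(200 × 100 / 300) = 2.858.
- Single arm at 100: 0.35 × √(100 / 2) = 2.475.
- Three groups at means 0, 0.35, 0.35: Σ(mᵢ − m̄)² = 0.0817, so λ = 8.17 at 100 and 7.68 at 94.

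| Reading | 100 per arm | 94 per arm |
|---|---|---|
| Pooled telecare v control, two-sided 5% | 81.3% | 78.8% |
| Nurse or peer v control, one-sided 5% | 79.4% | 77.2% |
| Three-group ANOVA, both telecare arms at 0.35 | 72.2% | 69.3% |
| Nurse or peer v control, two-sided 5% | 69.2% | 66.5% |

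**4. Detectable difference, one arm v control, two-sided, 80% power.** (1.960 + 0.842) × √(2/100) = 0.396. With 93.75 per arm, (1.960 + 0.842) × √(2/93.75) = 0.409.

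**The case against.** The strongest reply is that the document never promises 80% for nurse or peer support separately, so nothing it states has been shown false. The two-stage description of randomisation and the wording of the hypotheses both support the pooled reading, and there the figure is met at 100 per arm. This stands. A reader might infer that the sample size calculation is simply wrong, or that the plan claims 80% for each arm against control. The text supports neither, because it fixes no contrast.

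Three further points carry some weight:

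- **Sidedness.** The hypotheses are directional, and a one-sided 5% test of one arm gives about 79%. The document does not exclude this, but it does not state it either, and 95% intervals sit more naturally with a two-sided test.
- **Baseline adjustment.** The Baseline Data section implies that the questionnaires are also completed at baseline. An adjusted analysis would restore 80% for each arm if the baseline-outcome correlation were about 0.47 (100 per arm) or 0.52 (94 per arm). The article gives no such correlation. The adjustment model may sit in an analysis plan that is not shown.
- **Purpose.** The article calls the trial exploratory, and its third aim is to decide whether a full-scale trial is worthwhile. This lowers the stakes of a null result but does not remove the need to say what the 80% covers.

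None of these points answers the attrition error, which does not depend on the contrast chosen.

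**Conclusion.** The concern holds in a limited form, with moderate severity. The 80% is right at 100 per arm for pooled telecare against routine care (81%) and nearly right for an unstated one-sided single-arm test (79%). It does not carry over to two-sided comparisons of nurse or peer support with routine care (69%, about 11 points short), or to a three-group analysis of variance with both telecare arms at 0.35 (72%).

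The attrition allowance is wrong on any reading: 125 recruited gives about 94 analysed, not 100. At that number none of the four readings reaches 80%. The pooled contrast misses narrowly at 79%, while each arm separately is at 67% and the analysis of variance at 69%.

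The power figures rest on a standardised effect size, no baseline adjustment and no multiplicity adjustment. The attrition arithmetic needs none of these assumptions.

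**What to change.** In the Sample size section and the abstract, without changing enrolment:

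1. Name pooled telecare (nurse and peer together) against routine care, two-sided 5%, as the powered comparison. The hypotheses are already phrased this way.
2. Correct the attrition statement: 125 recruited per arm with 25% loss yields about 94 analysed per arm, and about 79% power for that comparison at an effect size of 0.35.
3. State that each supporter type against routine care has about 67% power, with a detectable difference of about 0.41 at 80% power.
4. Present nurse against peer as an estimate with a confidence interval.

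This costs wording only, and the stated power becomes less favourable. Keeping 100 analysed per arm instead would take 134 recruited per arm, which is 402 − 375 = 27 more patients.

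### The attrition allowance is miscalculated: 125 per arm less the stated 25% leaves about 94, below the plan's own minimum of 100 per arm

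*Protocol article*

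**What the plan says.** The Sample size section of the protocol article gives three figures in consecutive sentences.

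- The number needed: "A sample of at least 300 patients (minimum 100 in each arm) has been constructed to detect a difference in self-efficacy scores". It is tied to "an effect size of 0.35, 80% power at a level of 5% significance level", with 100 named as the minimum for each arm.
- The loss expected and the number to recruit: "Allowing for an attrition rate of 25% from initial recruitment, we will require 125 subjects in each arm (i.e. 375 participants in total".

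The Abstract (Methods/Design) repeats the recruitment target, "375 participants (125 in each arm) were sought from GP practices across West Midlands", without giving an attrition rate or the minimum of 100. No other section gives a different attrition rate or a different minimum.

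**The concern.** The 100 per arm is the number before the attrition allowance, so it is the number that must remain for analysis. The text takes the 25% loss from those recruited, so the allowance should be made by dividing by 0.75. The stated 125 is what results from adding 25% to 100, which is a different and smaller allowance.

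What is at stake is whether the design meets its own requirement. If attrition turns out exactly as assumed, the trial ends below the minimum to which its power claim is attached. Under Aims of the Trial, this study is also meant to inform a decision on a full-scale RCT, so an overstated attrition margin could be carried into the next design.

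**Working it through.** **Inputs** (all from Sample size)

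- Minimum for analysis: n = 100 per arm, 300 overall
- Attrition: d = 0.25 of those recruited
- Recruitment target: N = 125 per arm, 375 overall
- Standardised effect 0.35, power 80%, significance level 5%; neither sidedness nor the comparison powered is stated

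**Reproducing the stated 125**

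- Correct form: N = n / (1 − d) = 100 / 0.75 = 133.3, rounded up to 134. This does not give 125.
- Mark-up form: N = n × (1 + d) = 100 × 1.25 = 125. This gives the stated figure exactly.
- Correct form with d = 0.20: 100 / 0.80 = 125. This also gives it, but at an attrition rate the article does not state.

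**Back-check of the stated target**

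- Retained per arm: 125 × 0.75 = 93.75, about 94, against 100
- Retained overall: 375 × 0.75 = 281.25, about 281, against 300
- Shortfall: 100 − 94 = 6 per arm; 300 − 281 = 19 overall
- Largest attrition that 125 can absorb: 1 − 100/125 = 20%
- Target consistent with both the 25% and the 100: 134 per arm, 134 × 3 = 402 overall, which is 9 more per arm and 27 more overall

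**Effect on power**

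Power was computed from the noncentral t distribution with effect size 0.35 and significance level 5%. The noncentrality parameter is 0.35 / √(1/n₁ + 1/n₂), with n₁ + n₂ − 2 degrees of freedom. Because the article does not say which comparison or sidedness was used, three readings are shown.

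| Comparison (assumed) | 100 per arm | 94 per arm |
|---|---|---|
| One telecare arm vs control, two-sided | 69.2% | 66.5% |
| One telecare arm vs control, one-sided | 79.4% | 77.2% |
| Both telecare arms pooled (2:1) vs control, two-sided | 81.3% | 78.8% |

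The loss is between 2 and 3 points on every reading. A normal approximation gives slightly higher values (for example 69.7% and 67.0% in the first row) and the same loss.

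**The case against.** The best case on the other side concerns size, because the arithmetic itself is not in dispute.

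- *The effect is small.* A loss of 2 to 3 points of power biases no estimate and leaves the type I error untouched. On the pooled reading, the effect detectable with 80% power at 94 per arm is about 0.355, hardly different from the planned 0.35. This stands.
- *Attrition should not be blamed for the whole gap to 80%.* On a two-sided comparison of one telecare arm with control, power is already only 69.2% at 100 per arm, before any loss. Whether 100 per arm was the right starting point is a separate question; only 69.2 − 66.5 = 2.7 points of that gap belong here. This stands.
- *Crossing 80% depends on an assumption.* Power drops from above to below 80% only on the pooled two-sided reading. The hypotheses under Experiments Proposed Including End Points fit pooling; the second aim under Aims of the Trial fits separate arms. This stands, and the crossing is conditional.
- *The 25% might have been meant as a mark-up on completers.* This fails. The article calls it an attrition rate and takes it from those recruited, which makes 125 its base.

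None of these points removes the contradiction among 100, 25% and 125.

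**Conclusion.** The error is real. At its own attrition rate, the plan retains about 94 per arm (281 overall) and misses its own minimum of 100 per arm (300 overall). This follows from three stated figures and needs no outside assumption.

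The consequence is modest: about 6 analysable patients per arm and 2 to 3 points of power at an effect size of 0.35. The power figures assume equal arms, a standardised mean difference and one of the three comparisons shown above. A fall below 80% can be attributed to this error only if the pooled two-sided comparison was the one powered. The conclusion takes the 100 per arm as given and does not depend on how it was derived.

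**What to change.** Correct the sentence in Sample size. Two consistent versions are open.

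1. **Keep 375 recruited (preferred).** State that 125 per arm allows for 20% attrition, and that at 25% attrition about 94 per arm (281 overall) would be analysed. Give the power at 94 per arm, naming the comparison and the sidedness, since the figure could otherwise be 66.5%, 77.2% or 78.8%. The Abstract needs no change.
2. **Keep both the 25% and the minimum of 100.** The target becomes 134 per arm (402 overall), and the Abstract changes with it.

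The first costs one sentence and a slightly less favourable power figure, with no further patients. The second means 27 more participants, which is hard to justify for so small a gain when the Discussion already reports slow recruitment.
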